### Study design

This study adopts a non-randomized pre-/post-intervention design. Persons with a clinical diagnosis of MCI from treating health professionals will receive an 8-week group-based mindfulness training program which is customized to their needs, health outcomes and level of understanding. A follow-up assessment will be conducted one year after the program completion to measure the longitudinal effects of mindfulness practice on persons with MCI over time.

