### Research questions

Our hypotheses are:

That mindfulness practice will improve the cognitive function, psychological health, mindfulness and ADL functioning of persons with MCI.The degree of these improvements in cognitive function, psychological health, mindfulness and ADL functioning will correlate positively with the amount of mindfulness practice.

To test these hypotheses, the following quantitative research questions were formulated:

Does mindfulness practice improve the cognitive function, psychological health, mindfulness and ADL functioning of persons with MCI?Does the degree of improvement in cognitive function, psychological health, mindfulness and ADL functioning vary with the amount of mindfulness practice?How much of any observed improvement is due to formal mindfulness practice and how much is due to informal applications of mindfulness to ADL?

Further, this study aims to address the following qualitative research questions:

How do the MCI participants and familiar support persons (FSPs) engage with the mindfulness training program?What is the nature of group interactions between the Mindfulness Trainer and the MCI participants/FSPs and amongst the MCI participants/FSPs during the program?What is the mindfulness training program experience for the MCI participants and FSPs (e.g. was it enjoyable, satisfactory, stimulating and useful)?What perceived effects do the mindfulness training program and mindfulness practice generally have on the health and life of MCI participants and FSPs?What are the challenges faced by MCI participants in implementing and maintaining mindfulness practice?Do the expectations of the MCI participant and his/her FSPs about mindfulness practice match with each other?

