### Intervention

In addition to the standard care that the MCI participants obtain from their treating health professionals, they will receive the mindfulness training intervention. The intervention will be customized to the needs, health outcomes and level of understanding of MCI participants with a 1-year follow-up period. Participation in the 8-week group mindfulness training program will involve the MCI participants (preferably accompanied by their FSP) attending a 1.5-h group session, once weekly for a total period of 8 weeks. The MCI participants' attendance will be recorded and they are required to attend at least six of the eight sessions to have satisfactorily completed the program.

The program intervention will be designed, customized and facilitated either by a GP [name] (CH) or a Clinical Psychologist [name] (RC) who are experienced mindfulness experts and Monash University Mindfulness Consultants. They will be blinded to the identifiable data. The program includes both formal and informal mindfulness practices. Participants will be encouraged to practice formal mindfulness meditation techniques starting with 10 min twice a day and increasing this time up to 20 min twice a day as the program progresses. The formal mindfulness practice involves using techniques such as “body scan” and “breath” meditations to observe and maintain attention on an object of meditation without judgment and reactivity even when one becomes distracted by drifting thoughts or uncomfortable emotions. Informal mindfulness practice involves extending such attentiveness and awareness to engaging daily experiences such as mindful walking and eating. The informal practice will also include mental exercises such as reading, puzzles and language as well as being mindful of daily interactions and other ADL. Participants will also explore how mindfulness can help with attention and memory, ADL functioning, stress, anxiety and depression, emotion management, learning, mental flexibility and problem solving, and sleep with in-class and home practices (see Table 1 for a more detailed program outline).

**Table 1 T1:** **Customized 8-week group-based MCI mindfulness training program outline**.

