## Anticipated results

Repeated measures analysis of variance will be used to test the relative effects of formal and informal mindfulness practices on changes in the following dependent variables, namely cognitive function, psychological health, mindfulness, and ADL functioning from pre- to post-intervention and from post-intervention to 1-year follow-up, with an experiment-wise error rate of 0.05. Normally, each ANOVA should be evaluated with an adjusted (for e.g., Bonferroni correction) decision-wise error rate for possible inflation of Type I error. However, Type I error rate will not be adjusted for these analyses, on the grounds that this is an exploratory study of which any possible effects should be examined by further research. Regression analysis will be used to determine the predictive values of measures of formal and informal mindfulness practices on the changes in the same dependent variables (cognitive function, psychological health, mindfulness, and ADL functioning). Age, gender, and education will be entered into the regression analysis to identify possible moderating effects. The MCI participants' demographics, health and lifestyle information will be examined in relation to the outcome measures in order to interpret the results in context. However, possible trends instead of statistically significant results could be determined from the quantitative analysis. As such, the mixed-methods design of this study enables the qualitative findings to complement the quantitative results in greater depth so that their findings could inform each other and be integrated to better address the research questions. The IBM Statistical Package for the Social Sciences software package will be used for the statistical analysis of the quantitative data.

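### Research question 3 asks for shares of the improvement, but a one-group regression on amount of practice can only show whether those who practise more change more

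*Protocol article*

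**What the plan says.** Under Research questions, the second quantitative question asks whether the degree of improvement will "vary with the amount of mindfulness practice". The third goes further: "How much of any observed improvement is due to formal mindfulness practice and how much is due to informal applications of mindfulness to ADL".

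Under Anticipated results, two analyses touch on the two practices. One is an ANOVA: "Repeated measures analysis of variance will be used to test the relative effects of formal and informal mindfulness practices on changes". The other is a regression: "Regression analysis will be used to determine the predictive values of measures of formal and informal mindfulness practices on the changes". Age, gender and education also enter the regression.

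The Study design section states "This study adopts a non-randomized pre-/post-intervention design". Under Intervention, "The program includes both formal and informal mindfulness practices", and the formal home target is common to all: "starting with 10 min twice a day and increasing this time up to 20 min twice a day as the program progresses". Table 1 gives one weekly programme for everyone. The target sample is about 20 participants (Potential pitfalls and counteracting measures).

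**The concern.** Questions 2 and 3 have different targets. Question 2 is about differences between people: do those who practise more improve more? Question 3 is about the mean: of the average gain, what part did each practice produce? A regression of change on amount of practice addresses the first. Its null hypothesis is a zero slope between persons, and rejecting or not rejecting that null says nothing direct about shares of the mean.

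The differential effects of the two practices are among the aims in the abstract, and the emphasis on informal practice is presented in the Introduction as an advance on earlier work. If the regression is read as the answer to question 3, a practice with little spread between participants could be set aside because it shows no detectable predictive value, although it may have contributed to the gain.

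**Working it through.** **Step 1: what in the design could separate the practices.** There is no control group, no allocation to a practice type, and no formal-only or informal-only group or period. The time effect in the ANOVA combines both practices with retest gain and natural change. The only remaining contrast is the difference between participants in how much of each practice they do. That contrast is observational, because it depends on who chooses, or is able, to practise.

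**Step 2: from slope to share.** To turn a slope into a share of the mean gain, one must take slope × mean practice. This assumes that the effect is linear down to zero practice and that the amount of practice is unconfounded. The article states neither assumption.

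**Step 3: how informative the slope would be.** The article gives neither the spread of practice nor the SD of change, so these inputs are assumptions:
- n = 20 (the article's target); two-sided alpha 0.05 (from the article)
- five predictors: formal practice, informal practice, age, gender, education; residual df = 20 − 6 = 14, critical t = 2.145
- residual SD of change = 1; mean formal practice scaled to 1; gain = 0.5, all from formal practice and proportional to it, so the true slope is 0.5
- predictors independent; coefficient of variation (CV) of formal practice varied

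Approximate formulas:
- Slope: with four other predictors, the expected residual sum of squares of formal practice is (20 − 1 − 4) × CV² = 15 × CV². Hence SE ≈ 1/(CV × √15), non-centrality = 0.5 × CV × 3.873, and 95% half-width ≈ 2.145/(CV × 3.873).
- Paired test: SD of change = √(1 + 0.25 × CV²), d = 0.5/SD, non-centrality = d × √20, df = 19.

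| CV | Slope non-centrality | Slope power | Half-width of gain attributed to formal practice (SD) | d, paired test | Paired power |
|---|---|---|---|---|---|
| 0.3 | 0.58 | 8% | 1.85 | 0.494 | 56% |
| 0.5 | 0.97 | 15% | 1.11 | 0.485 | 54% |
| 0.7 | 1.36 | 24% | 0.79 | 0.472 | 52% |
| 1.0 | 1.94 | 44% | 0.55 | 0.447 | 48% |

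Simulation of the same model agrees. Slope power is 8–9%, 15–16%, 24–25% and 41–43%, and paired power is 46–48% at CV 1.0. The mean slope is about 0.5 at every CV and interval coverage is about 95%. The estimate is therefore unbiased, but at CV 0.3 its interval reaches about 1.8 SD on either side of a gain of 0.5 SD.

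**Step 4: benefit that does not depend on amount.** In a second simulation formal practice gave a full 1.5-point benefit whatever the amount done. The mean slope was 0.01 and it was rejected in 5% of runs, the false-positive rate. Here the slope is correctly near zero, yet the practice produced most of a mean gain of 2.0 points.

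**Step 5: comparing the two practices.** Let both contribute 0.5 SD, with CV 0.25 for formal and 0.75 for informal. Formal is significant in 7–8% of runs and informal in about 27%. Informal has the larger absolute t in 69–71%. With CVs of 0.4 and 0.6 that figure is 59%, where no distortion would give 50%. Comparison by p-value, standardised beta or R-squared thus favours the practice that varies more.

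**The case against.** The strongest reply is that the regression is the right tool for question 2 and that the article claims only predictive value for it. On this view the fault is in the wording of question 3 and in the limits of a one-group design, not in the choice of regression. That stands, and the fix is directed at the wording.

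A reader might infer that an effective practice will look ineffective. The documents do not support that. A common target is not common adherence: the article says "Participants will be encouraged to practice formal mindfulness meditation techniques starting with 10 min twice a day", collects practice records, and foresees more frequent contact for some participants. Its second hypothesis presupposes variation. If practice varies widely (CV about 1.0), the slope test is nearly as powerful as the paired test. A linear effect is also estimated without bias; it reads as absent only if non-significance is taken to mean no effect.

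A reader might also infer that the answer would mainly reflect which practice varied more. That depends on the ratio of the spreads and on a metric the article does not name. In the CV 0.25 against 0.75 example, ranking by the absolute raw slope puts formal, the less variable practice, first in 66–68% of runs. Nor does the article say that nobody will stop practising, so it cannot be asserted that there are no observations near zero practice.

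The exploratory label and the warning that significance is unlikely cover sample size and Type I error. They do not cover the mismatch: a larger sample would narrow the slope's interval but would not turn the slope into a share of the mean.

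**Conclusion.** The point holds as a mismatch between question and analysis. Question 3 asks for an apportionment that neither the design nor the regression can supply; the regression estimates an association between persons. This conclusion needs no numerical assumption.

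How weak the regression might be does rest on assumptions: n = 20, five predictors, a 0.5 SD gain proportional to formal practice, and a spread of practice that the article does not state. Over CVs of 0.3 to 1.0 the slope's power runs from about 8% to 41–44%, against about 56% falling to 46–48% for the mean gain. A practice with little spread may therefore show no detectable predictive value even if it works. Whether that will happen in this study cannot be told from the article. Severity is minor, since the study is declared an exploratory pilot.

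**What to change.** Reword question 3 as: *Is change associated with differences between participants in the amount of formal and of informal practice?* It then extends question 2 by type of practice.

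Under Anticipated results, add that improvement will not be apportioned between the practices and that a non-significant slope is not evidence that a practice contributes nothing.

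As secondary reporting detail, give each unstandardised slope with its 95% confidence interval beside the mean and SD of that practice, and do not compare the practices by p-value, standardised beta or R-squared.

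The cost is a few sentences and no new data. The study does give up the claim to divide the improvement between the two practices.

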**Figure 2 F2:**
[figure not shown]
**Framework of the presentation of qualitative and quantitative data**. ADl, Activities of Daily Living; ANOVA, Analysis of variance; FSP, Familiar Support Person; MCI, Mild Cognitive Impairment.

The MCI participants and FSPs have the option to receive an email containing a summary of the non-identifiable group results when this study is completed. The findings from this study will be disseminated through peer-reviewed academic journal publications and presented at national and international seminars and conferences. In any publication and presentation, the information will be presented in non-identifiable form to protect the privacy of the MCI participants and their FSP.

It is expected that the mindfulness training intervention will proactively engage the MCI participants early and yield the practical application of improving their cognitive function such as attention and memory if they maintain mindfulness practice over time. There may be a potential benefit of delaying the progression of MCI to AD but this will not be assessed in this study. In addition, other expected improvements in psychological health, mindfulness, and in functional abilities of ADL may also indicate better health outcomes of mindfulness for MCI. This study will contribute toward the clinical research of MCI and advance evidence-based knowledge about the effects of long-term mindfulness practice as a promising and feasible non-pharmacological therapeutic approach for persons with MCI. This could potentially translate to downstream significance of better quality of life and higher work productivity of persons with MCI and their FSP, and a reduced chronic disease burden on families of persons with MCI and the healthcare system. If effective, “partnerships could be eventually forged with the Alzheimer's Australia and memory clinics/services such as the CDAMS to deliver the customized group mindfulness training program to the target population of persons with MCI and their FSP” (Wong et al., 2015).

The study findings could open a potential future research direction to explore the use of biomarkers such as beta-amyloid and tau proteins to monitor the longitudinal effects of mindfulness practice on the cognitive and functional progression of persons with MCI and the conversion rate from MCI to AD.

## Potential pitfalls and counteracting measures

This study was originally designed as a randomized controlled trial using pre- and post-intervention design that will assign persons who have been clinically diagnosed with MCI to either the 8-week mindfulness training intervention group or the “standard care” control group. In the original randomized controlled trial design, the estimated total sample size is 166–83 MCI participants in the intervention group and 83 in the control group, in order to achieve 80% power for a two-tailed test at the alpha level of 0.05 with a medium effect size of 0.50. The minimum sample size required to detect a clinically significant difference is 68 participants–34 in each of the two groups. This design was approved by the Melbourne Health Human Research Ethics Committee. However, due to the challenges in the study recruitment of MCI participants, changes had to be made to the randomized controlled trial study design to that of a pilot study that would explore the feasibility of the mindfulness training intervention for future research. Consequently, the revised target sample size is about 20 MCI participants. An estimation of 80 interviews conducted with 20 MCI participants and 20 FSPs at T1 and T2, and coupled with participant observation of the mindfulness program produce rich qualitative data and provide important participant perspectives such as learning and maintaining a new behavior, that could yield significant contributions to the field (Morse, 2000; Creswell, 2007), especially in this sub-clinical population that is under explored. The findings would be relevant to better understand this population, help future study recruitment, and shed insights to further research studies with this population. This revised study design was also approved by the Melbourne Health Human Research Ethics Committee.

As the age profile of the MCI participants is senior (at least 60 years old), program attendance and participation might be affected by various circumstances such as clinically significant scores of cognitive impairment measured by MoCA and of psychological health measured by DASS-21, conversion to dementia such as Alzheimer's disease, and pre-existing medical conditions. The research team will review the participants' continued study participation and notify their GP or treating health professional for follow-up after discussion with them.

The MCI participants are required to attend at least six of the eight sessions to have satisfactorily completed the mindfulness training program. The MCI participants and FSPs are provided with the program manual and the mindfulness practice audio CD, and researcher (WW) contacts the MCI participants weekly during the program duration to discuss any questions, concerns and issues that they might have. WW will also inform the outline of the weekly module to those who have missed the session.

To encourage the MCI participants to do their mindfulness practices and obtain their monthly practice record forms, researcher (WW) will contact them on a monthly basis after their completion of the mindfulness training program. However, due to the extent of cognitive impairment of certain MCI participants, particularly for those who are not living with their FSP, WW might have to contact them more frequently to better support them. Such study rigor might impose some inconvenience on these MCI participants. Thus, WW will check with them on their comfortable frequency of post-intervention communications such as fortnightly phone calls.

The MCI participants and FSPs are free to withdraw consent from the study at any stage by informing the research team which will still include the previous data and information that are already collected from them in the data analyses to form part of the study findings.

While the study findings from this reasonably homogeneous sample may be potentially positive, however, due to the small sample size, it is not likely to reach statistical significance. As such, the study will also share the similar study limitation of small sample sizes in previous studies and its results may not be generalizable to the broader community.

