At the first data collection session, another opportunity is open for the potential MCI participant and FSP to ask further questions, and seek any clarification about this study and the nature of their involvement. Researcher (WW) will review and discuss this study and the Participant Information Sheets and Consent Forms with the potential MCI participant in the presence of his/her FSP and decide whether he/she is able to:

Understand the nature of the research and of his/her participation;Appreciate the consequences of the participation, including personal consequences;Show the ability to consider alternatives, including the option not to participate; andshow the ability to make a reasoned choice (Lyketsos et al., 2004).

If the potential MCI participant is able to paraphrase the information that has been provided and is aware of his/her rights to refuse or discontinue participation, this will be seen as indicating capacity to consent. Prior to study participation, the potential MCI participant must be able to give his/her free voluntary written informed consent to participate by signing the Consent Form in the presence of his/her FSP who will also confirm his/her capacity to decide study participation and support his/her participation. The FSP will also be asked to provide his/her written informed consent by signing the Consent Form. The MCI participant is recommended to advise his/her GP of his/her decision to participate in this study.

The recruitment of the MCI participant with his/her FSP is preferred but not mandatory. The FSP can be a family member, guardian or person authorized by law, and must be at least 18 years old with no English language difficulties. He/she can confirm the MCI participant's capacity for informed consent, and can provide information about the MCI participant's functional abilities, and demographics, health and lifestyle details. The knowledge of the FSP about the MCI participant is crucial to corroborate the MCI participant's capacity for informed consent and then provide information that could add value to the data. The FSP is required to be present with the MCI participant during the first data collection session to witness the consent process, and is also encouraged to attend the second and third data collection sessions, and the 8-week group mindfulness training program together with the MCI participant.

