#### Qualitative data

Qualitative data collection will involve participant observation of the 8-week group mindfulness training program and individual semi-structured interviews conducted separately with the MCI participant and his/her FSP. The recruitment target of which qualitative data saturation with no new discoveries is anticipated to be about 20 MCI participants.

Researcher (WW) will attend all the eight sessions of the group mindfulness training program to conduct participant observation in order to evaluate how the MCI participants and FSPs engage with the program, particularly with the core modules of “attention and memory,” “ADL functioning,” “stress, anxiety and depression,” “emotion management,” “learning, mental flexibility and problem solving,” and to assess the nature of group interactions between the Mindfulness Trainer and the MCI participants/FSPs, and amongst the MCI participants/FSPs during the program. Notes will be recorded during and following the observation for subsequent qualitative data analysis.

Semi-structured interviews will be conducted by researcher (WW) during the data collection sessions at post-intervention (T2) and 1-year follow-up (T3). During each of these two data collection sessions, separate interviews with the MCI participant and his/her FSP will be done after the MCI participant has completed the cognitive assessment and questionnaires/scales. These interviews aim to elicit responses from individual perspectives of the MCI participant and his/her FSP in relation to their own mindfulness training program experience; the perceived effects of the program and mindfulness practice have on the health and life of MCI participants and FSPs; the challenges faced by the MCI participants in implementing and maintaining mindfulness practice; and the expectations of the MCI participants and FSPs about mindfulness practice. The interview questions for the MCI participant at T2 and T3 are appended in Table 2; and the separate set of interview questions for the FSP at T2 and T3 is appended in Table 3. In the event of the FSP's unavailability during T2 and/or T3 data collection sessions, arrangements can be made for the interviews to be conducted over the phone. All the interviews will be recorded on a digital audio recorder to ensure accurate representation of responses, and transcribed verbatim by researcher (WW).

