## Stepwise procedures

Altogether, there are a total of 3 data collection sessions in this study, which will be held at any of the Monash University campuses or a public venue such as library and community club that is convenient to the MCI participant and his/her FSP. The MCI participant will be administered the MoCA, the 21-item DASS-21, the 14-item FMI and the 12-item MAQ by researcher (WW) during these data collection sessions at three time points:

Pre-intervention (T1);Post-intervention (T2); andOne-year follow-up (T3).

These measurements should take about 30 min each session and will be conducted to compare the effects of mindfulness on the outcomes measures across these time frames and to determine whether any changes are sustained over time. By incorporating a 1-year follow-up into the study design, it could more effectively measure the longitudinal effects of mindfulness practice on persons with MCI over time. A semi-structured interview with the MCI participant that should take about 30 min, will be conducted by researcher (WW) at T2 and T3 after he/she has completed the above-mentioned cognitive assessment and questionnaires/scales.

The nature of the participants' MCI condition could possibly fluctuate between the time frames of provision of written informed consent (with their capacity to consent as confirmed by their FSP) and the 1-year follow-up period. In other words, their MCI condition could remain stable, improve or deteriorate to AD during the study duration. In the event that the MCI participant's MoCA score suggests severe cognitive impairment, his/her continued study participation will be reviewed and the referral to his/her GP or treating health professional for follow-up will be discussed with him/her and his/her FSP. Likewise, if the MCI participant reports a clinically significant DASS-21 score, the research team will contact him/her to ensure his/her well-being and seek his/her permission to inform his/her FSP and forward the score to his/her GP or treating health professional for follow-up. Any clinically significant information about the MCI participants collected from their study participation, will be stored in their health records with the participating CDAMS sites or communicated to their GP or treating health professional.

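### A research question compares participants' and support persons' expectations, but neither interview guide asks about them; the 80 interviews are also placed at T1 and T2, against T2 and T3 elsewhere

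*Protocol article*

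**What the plan says.** Three parts of the protocol article bear on this.

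- **The question.** The last of the six qualitative questions under Research questions is: "Do the expectations of the MCI participant and his/her FSPs about mindfulness practice match with each other". The Abstract lists expectations among the qualitative aims. The Qualitative data section names the expectations of both parties as something the interviews are meant to draw out.
- **The instrument.** Tables 2 and 3 are presented as the interview questions for participant and FSP. Table 2 has 12 numbered items and Table 3 has 8, with prompts and separate T2 and T3 wording where the two differ.
- **The timing.** Under Qualitative data: "Semi-structured interviews will be conducted by researcher (WW) during the data collection sessions at post-intervention (T2) and 1-year follow-up (T3"). Under Potential pitfalls and counteracting measures, after the statement that "the revised target sample size is about 20 MCI participants", the article estimates "80 interviews conducted with 20 MCI participants and 20 FSPs at T1 and T2".

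On the FSP, the Recruitment section says: "The recruitment of the MCI participant with his/her FSP is preferred but not mandatory".

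**The concern.** A question about whether two people's expectations agree needs the same thing asked of both members of each pair. If the guides do not ask it, whether a pair contributes data depends on what one interviewer happens to probe in each of two separate conversations. Some pairs may then have a statement from one side only.

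The time-point conflict adds to this. A reader of the pitfalls section would believe that interviews take place before the program and could record expectations at that stage. The methods contain no such interview, so anything said about expectations is first recorded after eight weeks of training. Pre-program expectations that are not collected at the time cannot be recovered later.

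**Working it through.** **1. Reproduce the stated count.** Inputs, from the pitfalls section: 20 participants, 20 FSPs, two interview time points. (20 + 20) x 2 = 80, as stated. With T2 and T3 in place of T1 and T2 the sum is the same, 80. The slip is in the labels and not in the arithmetic. Interviews at all three visits would give 40 x 3 = 120, so the article does not mean three rounds.

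**2. Set the timing statements side by side.** Stepwise procedures defines the visits: "Pre-intervention (T1);Post-intervention (T2); andOne-year follow-up (T3").

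| Place | Interviews at |
|---|---|
| Abstract, Methods | post-intervention and one year |
| Qualitative data | T2 and T3 |
| Headings of Tables 2 and 3 | T2 and T3 |
| Stepwise procedures, participant | T2 and T3 |
| Stepwise procedures, FSP | T2 and T3 |
| Potential pitfalls | T1 and T2 |

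Two further details favour T2 and T3. The FSP's time is put at about 30 minutes at T1, when the FSP completes the scale and the questionnaire, and about an hour at T2 and at T3. The pitfalls section also says the interviews will show how people take up a new habit and keep it up; keeping it up over the year can be seen only at T3, the visit which that section omits.

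**3. Check the guides item by item.**

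- Table 2, items 1 to 12: general health, program experience, likes and improvements, how mindfulness is practised, help and hindrance, how the person has been, perceived influence, intention to continue, need for support, advice to others, role of the FSP, other comments.
- Table 3, items 1 to 8: the experience of supporting, program experience, personal influence, improvements, how the participant has practised, influence and usefulness for the participant, own role, other comments.

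Items that ask about expectations: 0 of 12 + 8 = 20. The nearest are Table 2 items 8 and 9, which look forward to continued practice and support. Table 3 has no counterpart to either, so even these cannot be paired.

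**4. Show that 80 is a ceiling.** With F FSPs and no loss, the count is (20 + F) x 2. The article gives no expected F, so these values are assumptions:

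- F = 20: 80
- F = 15: (20 + 15) x 2 = 70
- F = 10: (20 + 10) x 2 = 60
- F = 0: (20 + 0) x 2 = 40

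Any loss before T3 lowers these further. The article itself foresees withdrawal, conversion to dementia and review of continued participation.

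**The case against.** The strongest reply is that the time-point error is an isolated slip. All other statements agree on T2 and T3, nobody following the methods would misplace an interview, and 80 is unchanged. That stands: taken alone, it is an editorial correction.

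The second reply is that the interviews are semi-structured, expectations are a declared aim for both parties, and the analysis is inductive. A reader might infer from the empty guides that the sixth question cannot be answered. The article does not support that, because probing may bring expectations out. What remains is narrower: no item is dedicated to the topic or matched across the pair. This is not detail that a condensed article leaves out, since the tables are presented as the interview questions, item by item.

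Third, a reader might infer that the question concerns expectations held before the program. The article does not say so. Practice continues for a year after the program, so expectations voiced at T2 are still about something to come. A T1 record is therefore an improvement and not the correction of an error.

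Fourth, a reader might infer that the 80 interviews are what justify 20 participants. The stated reason for the change of design is "due to the challenges in the study recruitment of MCI participants", and the Qualitative data section separately anticipates saturation at about 20. The interview count is added support and is labelled an estimation.

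Finally, any figure below 80 rests on assumed FSP numbers, and the article has safeguards: telephone interviews for an FSP who cannot attend, and a search for a replacement if one withdraws. These stand as reasons not to put forward a specific lower yield. They do not make 80 more than a maximum.

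**Conclusion.** The point holds in two parts of unequal weight. The main one is that a stated research question, repeated as an interview aim, has no item behind it in either guide (0 of 20), and the nearest forward-looking items exist for the participant only. Matched data on expectations are possible but not assured. This rests on reading the tables as the guides in use, which is how the article presents them.

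The lesser part is a certain contradiction: T1 and T2 in one place, T2 and T3 everywhere else. It does not alter the count of 80, and the sample size does not depend on it. Its practical meaning is that no interview precedes the program. That 80 is an upper limit follows from the optional FSP and possible loss by one year; how far below 80 the yield would fall cannot be said from the article.

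**What to change.** 1. Add one expectation question, worded identically, to the participant guide and the FSP guide.
2. Preferably, also ask both parties a brief written version at T1, which the FSP is already required to attend, so that expectations are on record before the program starts.
3. If neither is wanted, remove the sixth qualitative question and the expectations wording in the Abstract and the Qualitative data section.
4. In the pitfalls section, change the count to up to 80 interviews at T2 and T3.

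The cost is a few minutes at a visit that already takes place, one line in each guide and a minor ethics notification. The stated interview yield will look slightly less favourable.
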